### Study design and population

The study was an observational study using qualitative (i.e. semi-structured interviews) and quantitative methods (i.e. questionnaires and logbooks), allowing data triangulation to evaluate the dissemination process of DOiT at 20 prevocational education schools in the Netherlands. As part of the process evaluation of the dissemination, a cluster-controlled designed study with ten control schools, matched on level of education, location (rural/urban area) and school size, was conducted to evaluate the effectiveness of implementation of DOiT on anthropometrics and EBRBs of adolescent students. Students were recruited via the schools, so no individual contact information was needed. At each school, three classes were invited to participate, i.e. all students and their parents. At least two weeks prior to the commencement of the study, parents and students received an information letter explaining the background, aim and procedures of the study. There were no individual inclusion or exclusion criteria for study participation. When students moved to another school, they were not included in the follow-up measurement.

The Medical Ethics Committee of the VU University Medical Center approved the study protocol in which we applied for a passive consent procedure for parents, students and teachers. A passive consent procedure means that students or parents who did not want to participate in the study could send a letter to the researcher should they choose to decline participation. Students who declined for participation were excluded from the measurements. The study protocol adhered to the RATS guidelines.

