### Data collection procedures

#### Recruitment of schools

We aimed to include 20 DOiT implementation schools in the process evaluation. This number was based on feasibility and also a similar study, conducted in the Netherlands, evaluating the dissemination process of a Dutch healthy diet program, the Krachtvoer evaluation study [20].

After a school ordered the DOiT materials, the school was invited to participate in the study. The school was then informed about the study protocol by telephone and written information. If the school agreed to participate, the researcher visited the school in order to explain the procedures. Participating schools needed to meet the following criteria: (1) willing to implement DOiT during two subsequent school years; (2) a signed agreement of participation in the study during that period (2011–2013); (3) willingness to appoint a DOiT coordinator who was the linking agent between the research team and the school; (4) being able to participate with at least three classes of the first two years of their prevocational education, and (5) willingness to provide space and time for measurements. All teachers involved in the implementation of DOiT were asked to participate in the process evaluation. If schools participated in the study, they received free materials for three classes and a short report of the research results upon completion.

Regarding the process indicator effectiveness, 510 students per group were needed to detect a relevant difference in body mass index (BMI) between the intervention and control groups. Therefore, ten control schools were needed. Taking into account the clustered design, missing data and dropout (25%), a sample size of 1274 students were required to conduct multi-level analyses with an estimated power of 90% and an alpha level of significance set at 0.05 (see Table 4).

**Table 4 T4:** Number of subjects needed to detect a relevant difference between DOiT and control schools

**Outcome**	**sd**	**Difference**	**Number of subjects***	**Number of subject including 25% dropout**
BMI	1.2	0.25 kg/m^2^	510	637
Waist circumference	3.9	2 cm	80	100
Sum of skinfolds	14.6	5 mm	180	224
Sugar-containing beverages	840.4	250 ml/day	238	297
Sedentary behaviour	147.5	30 minutes/day	508	635
Active transport	23.3	10 minutes/day	115	143
Snacks	1.4	1 portion/day	40	51

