### Analyses

Our first aim is to evaluate the nationwide dissemination process of DOiT in the Netherlands All qualitative data systematically collected or observed during the study will be considered as data [29,30]. This means that not only information from in-depth interviews with teachers, but also all data reported during phone calls or observed during school visits will be included in the analysis. Regarding the interviews, a literal transcript of the audiotape of each interview will be written. All transcripts and other data will be marked with codes (open coding). The codes will be grouped into similar concepts in order to make them more workable, i.e. selective coding. Using tables and matrices, we aim to identify and compare facilitators and barriers around the key process indicators and implementation-related determinants. All quantitative data obtained from the logbooks and the teacher questionnaires collected during the study will be analysed in SPSS 20.0 (SPSS Inc. Chicago, Illinois, USA).

Our second study aim is to examine the relationship between quality of implementation and changes in students’ EBRBs and anthropometrics. The change in students’ EBRBs and anthropometrics will be analysed using multi-level linear regression analysis. We define three levels in our multi-level analyses: 1) student, 2) class, and 3) school. Analyses will be adjusted for baseline values, age, gender, ethnicity, and educational level. These variables will be checked as potential effect modifiers. Multilevel statistical analyses will be performed using MLwiN 2.22.

The process data, including information on level of dosage, level of fidelity and quality of delivery, will be combined into an ‘school implementation score’. Using linear regression analysis, we will examine the association between quality of implementation (implementation score) and program effect on EBRBs, as well as on anthropometrics. For all analyses a two-tailed significance level of <0.05 will be considered statistically significant.

In addition, we will explore the behavioural mediators of the intervention effect on BMI, waist circumference and sum of skinfolds using the product-of-coefficient method of MacKinnon [31]. We will specifically look at the mediating effects of consumption of sugar-containing beverages; consumption of high sugar/high fat snacks; sports participation; active transport; screen time and breakfast behaviour.

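### Table 4 allows for 25% dropout by multiplying by 1.25 instead of dividing by 0.75, so the total of 1274 covers about 20% loss and leaves 478 per group for BMI against the 510 required.

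*Protocol article*

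**What the plan says.** Under Recruitment of schools, the protocol article states that "510 students per group were needed to detect a relevant difference in body mass index (BMI") between intervention and control. It then says that, allowing for clustering, "missing data and dropout (25%), a sample size of 1274 students were required", with "an estimated power of 90% and an alpha level of significance set at 0.05". The Analyses section makes the test two-sided: "For all analyses a two-tailed significance level of <0.05 will be considered statistically significant".

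Table 4 gives, for seven outcomes, an sd, a difference, a base number of subjects and a last column headed "Number of subject including 25% dropout". The BMI row reads "BMI 1.2 0.25 kg/m^2^ 510 637". Twice 637 is 1274, so the total in the text is the BMI entry of the last column, doubled.

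The design itself is not balanced by school. The process evaluation has 20 implementation schools, a number set on feasibility and on a similar study, and there are ten control schools. Under Study design and population: "At each school, three classes were invited to participate".

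**The concern.** If a quarter of the enrolled students are lost, three quarters remain. Enrolment must then be the required number divided by 0.75. Adding 25% to the required number is a different operation and gives a smaller figure. The last column of Table 4 appears to use the second operation while its heading claims the first.

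If so, the stated enrolment does not yield the stated number for analysis at the plan's own dropout rate, and the power stated for BMI, the outcome that sets the total, is not reached. The single total also hides how many students each arm was meant to have.

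**Working it through.** **Inputs.** From Table 4: base n, sd, difference and the number including dropout for each outcome. From the text below the recruitment criteria: 510 per group, 25% loss, 1274 in total, power 90%, alpha 0.05. From Analyses: two-sided testing.

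**Step 1: reproduce the plan's figure.** 510 × 1.25 = 637.5, printed as 637; 2 × 637 = 1274. The plan's total is reproduced by multiplication. Division gives 510/0.75 = 680 per group and 1360 in total, which does not reproduce it.

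**Step 2: apply both rules to every row.**

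| Outcome | Base n | n × 1.25 | Printed | n/0.75, rounded up | Printed × 0.75 |
|---|---|---|---|---|---|
| BMI | 510 | 637.5 | 637 | 680 | 477.75 |
| Waist | 80 | 100 | 100 | 107 | 75 |
| Skinfolds | 180 | 225 | 224 | 240 | 168 |
| Beverages | 238 | 297.5 | 297 | 318 | 222.75 |
| Sedentary behaviour | 508 | 635 | 635 | 678 | 476.25 |
| Active transport | 115 | 143.75 | 143 | 154 | 107.25 |
| Snacks | 40 | 50 | 51 | 54 | 38.25 |

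Multiplying by 1.25 matches every printed entry to within one subject; dividing by 0.75 matches none. The differences of one subject are rounding. Taking the unrounded two-sample size 2 × (sd × (1.960 + 1.282)/difference)² and multiplying by 1.25 gives 224.0 for skinfolds, 296.8 for beverages, 142.6 for active transport and 51.5 for snacks, against the printed 224, 297, 143 and 51. The slip is therefore systematic and not a misprint.

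**Step 3: what 1274 protects against.** 1 − 510/637 = 19.9%. At 25% loss, 637 × 0.75 = 477.75, about 478 per group, 32 below 510. In total, 1274 × 0.75 = 955.5 against 2 × 510 = 1020. The enrolment is short by 1360 − 1274 = 86.

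**Step 4: which outcomes miss their requirement at 1274.** With 478 per group, waist (80), skinfolds (180), beverages (238), active transport (115) and snacks (40) are all well covered. BMI (510) and sedentary behaviour (508) are not.

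**Step 5: power before clustering, equal groups.** Normal approximation: power = Φ(difference/(sd × √(2/n)) − 1.96).

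- BMI, printed sd 1.2, n = 478: 0.25/(1.2 × √(2/478)) = 3.22, power 89.6%.
- BMI, sd implied by 510. The printed sd of 1.2 gives 485, not 510. The unrounded ratio is 1.053, so the sd that returns 510 is 1.2 × √1.053 = 1.23. At n = 478 the power is 88.0%.
- Sedentary behaviour, n = 476 (635 × 0.75, the row on its own): 30/(147.5 × √(2/476)) = 3.14, power about 88%. This figure needs no inferred sd, because the printed inputs return the printed 508 to within rounding.

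**Step 6: the split.** 1274 = 2 × 637 presumes equal arms, whereas the schools are 20 and 10. Two readings, both assuming equal class sizes, three classes per school and 25% loss:

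- 1274 is the overall total: about 425 controls and 849 intervention students enrolled, 319 and 637 analysed. BMI power before clustering is about 86% (sd 1.2) or 84% (sd 1.23).
- 637 is the control target and the 20 schools contribute twice that: 637 + 1274 = 1911 enrolled, about 478 and 956 analysed. This has the precision of 2 × 478 × 956/(478 + 956) = 637 per group. BMI power before clustering is about 96% (sd 1.2) or 95% (sd 1.23).

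**The case against.** The strongest defence is that the slip has little effect. It costs between 0.4 and 2 points of power, five of seven outcomes are unaffected at the total of 1274, and data collection ended in June 2013, so recruitment cannot change. One could also read the 25% as a surcharge on the required number. The point about size stands and limits the weight of the finding. The surcharge reading does not rescue the label: the heading and the sentence both present 25% as dropout, and a 25% surcharge is an allowance for 20% dropout.

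Three stronger readings are tempting, and the document does not support them.

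- A reader might infer that the total fails every outcome because every row is wrongly inflated. It does not: at 478 per group only BMI and sedentary behaviour fall below their stated numbers.
- A reader might infer that the control arm needs at least 680 students. That is a figure for equal groups. With a 2:1 split, 383 controls and 765 intervention students analysed have the precision of 510 per group (2 × 383 × 765/1148 = 510), so about 510 controls enrolled (383/0.75 = 511) would do.
- A reader might infer that the trial had only about 319 controls for analysis. That holds only if 1274 is the overall total. The text moves from the per-group requirement directly to the need for ten control schools, and sets the 20 implementation schools separately. This fits about 637 controls at least as well, and that reading gives about 95% to 96% power before clustering.

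**Conclusion.** The dropout allowance is wrong as written. Table 4 and the total of 1274 are inflated by 1.25, which covers about 20% loss; at the stated 25% the plan keeps about 478 per group for BMI, 6% below the 510 it requires, and 476 against 508 for sedentary behaviour if that row is sized by itself. Power falls from 90% to between 88.0% and 89.6% for BMI and to about 88% for sedentary behaviour.

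These power figures assume equal arms, exactly 25% loss and no clustering effect. They do not show that the trial was underpowered: the article does not say how 1274 was to be divided between 20 and 10 schools, and the answer moves BMI power more than the dropout error does (about 84% to 96% before clustering). What is established is a stated size that does not match its own label, and a total whose meaning for each arm is unclear.

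**What to change.** Correct the last column of Table 4 to n/0.75, rounded up: BMI 680, sedentary behaviour 678, beverages 318, skinfolds 240, active transport 154, waist 107, snacks 54. Change the total in the text to 1360. Alternatively, leave the numbers and state that they allow for 20% loss.

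In the same place, say whether 1274 is an overall total or two arms of 637, given 20 implementation and 10 control schools. As data collection has ended, report the power again from the numbers enrolled in each arm and the loss observed.

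The cost is one table column, one sentence and a short recalculation. The design and the analyses do not change. Under an equal split the stated power becomes slightly less favourable; with the actual arm sizes it may be lower or higher than 90% before clustering.

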#### Process measures

Process data were collected by teachers, DOiT coordinators, DOiT support office, students and parents throughout the whole research period.

#### Teachers

At baseline (T0), after eight (T1) and 20 months (T2), all teachers involved in the implementation of DOiT were asked to complete an online questionnaire about the impeding and facilitating factors of the implementation of DOiT. Completing the questionnaire took approximately 30 minutes. The majority of the questionnaire consisted of structured questions, measured on a bipolar five-point Likert scale. A few open-ended questions were added. The questionnaire was based on existing questionnaires, used in the previous DOiT evaluation [14,21] and the Krachtvoer evaluation study [22]. The questionnaire contained questions regarding the context, recruitment, satisfaction, maintenance, and potential relevant implementation-related determinants of the program. Additionally, the questionnaire contained items on other on-going studies and other innovations or school health-promotion programs. After each lesson teachers were requested to complete an online log. Completing the log took approximately 5 minutes per lesson. Using this log, we aimed to administer completeness of implementation by having teachers indicate if the lesson was taught, when it was taught and how the lesson was prepared and implemented. Teachers could tick off what activities were executed in preparation of the lesson on a list of proposed activities according to the teacher manual and how much time they spent on these activities. Teachers ticked off what materials were used during the lesson, what lesson activities were implemented and if the implementation complied with the prescription in the teacher manual. Finally, teachers reported how much time they spent in the classroom and rated their satisfaction with the lesson on a ten-point rating scale. Additionally to the questionnaires and logbooks, we aimed to visit each school at least once during the research period for a structured observation of a DOiT lesson.

#### DOiT coordinator at the schools

At the end of each school year (T1 and T2), i.e. in total twice during the research period, a sub-group of teachers and the coordinator were invited for an in-depth interview to gain more insight into the implementation of the DOiT program, its content, recruitment, fidelity and satisfaction with the dissemination strategy, and overall satisfaction with DOiT. Furthermore, facilitators and barriers for implementation, intentions and opportunities for future implementation of DOiT were discussed.

#### DOiT support office

During the recruitment period and the implementation period, the DOiT support office employee was requested to complete a log regarding all meetings, recruitment activities and communication with teachers and schools.

#### Non-adopting schools

After the recruitment phase, teachers that had not ordered the DOiT program were invited to complete a web-based questionnaire in order to gain insight into reasons for not implementing DOiT. The questionnaire contained questions regarding context and recruitment. Participants were invited by email to complete the questionnaire. Completing the questions took approximately 10 minutes.

#### Students

##### Questionnaire

Before the start of DOiT (T0) and after 20 months (T2), students were asked to complete the DOiT questionnaire in a classroom. The DOiT questionnaire addressed the following EBRBs: consumption of sugar-containing beverages; consumption of high sugar/high fat snacks; physical activity (sports and active transport); screen time (TV viewing and computer use) and breakfast behaviour. The questionnaire showed good test-retest reliability and moderate to good construct validity for the majority of items [23]. Since the item on physical activity (’hours of after school time physical activity at school’) showed a moderate test-retest reliability, we used the questions of the QAPACE questionnaire to assess physical activity [24]. Before the assessment, a researcher explained the procedures following a standardised protocol. Students needed approximately one school lesson (i.e. 45 minutes) to complete the questionnaire. After completing the measurements, students received a small incentive. At T2, we asked students to complete ten additional questions on their satisfaction with the program, their opinion about the content of the DOiT lessons and the layout of the DOiT materials. The questionnaire consisted of structured questions, measured on a ten-point rating scale.

##### Anthropometry

Before the start of DOiT (T0) and after 20 months (T2), we measured body weight, body height, skinfold thickness, waist and hip circumference. During PE lessons, anthropometric measurements were completed in the change-rooms. A separation structure was used to guarantee privacy during the measurements. The procedures of the measurements were explained to the students prior to any measurements being taken. Body weight was measured and recorded within 0.1 kg with a calibrated electronic flat scale (Seca 861), levelled after each placement. Body height was measured and recorded with an accuracy of 1 mm using a portable stadiometer. Skinfold thickness (i.e. triceps, biceps, suprailiac, subscapula) was measured on the left side of the body to the nearest 0.2 mm (Harpenden Skinfold Caliper) [25]. Two measurements were conducted. If the difference was more than 1 mm, a third measurement was taken. The skinfold thickness was taken as the average of the two nearest measurements. Both, waist and hip circumferences were measured with a Seca 206 waist circumference measure (Seca, Hamburg, Germany) to accuracy of 0.1 cm.

All student measurements (i.e. anthropometrics and questionnaire) were performed according to a standardised protocol by a trained research team during a 10-week period to minimise seasonal influences. The research team was not blinded to group assignment.

#### Parents

Before the start of DOiT (T0) and after 20 months (T2), parents were invited to complete an online questionnaire. Parents were reached via the school. Schools were asked to email the web link directly to parents. The questionnaire was based on the ENERGY parent questionnaire [26] and contained items on the physical home environmental, i.e. availability and accessibility of sugar-containing beverages and high sugar/high fat snacks, options for physical activity (sports and active transport), rules for screen time (TV viewing and computer use), availability and accessibility of breakfast products and availability of pocket money for food and drinks. The questionnaire mainly consisted of structured questions, measured on a bipolar five-point Likert scale. At T2, ten additional questions were asked about their satisfaction with DOiT (i.e. parental information booklet, homework assignments and parent meeting). Completing the questions took approximately 5 minutes.

#### School environment

Partly based on the audit instruments used in the ENERGY study [27] and the ENDORSE study [28], a DOiT audit instrument was developed to assess the availability and accessibility of foods and physical activity facilities in and around the school. Before the start of DOiT (T0) and after 20 months (T2), two researchers independently completed the audit instrument at each school. The audit instrument consisted of five parts: (1) food/drink available in the canteen; (2) food/drink available in vending machines; (3) physical activity facilities; (4) bicycle parking; and (5) available food retail outlets around school. For the majority of the items, the audit instrument had a ‘tick box’ answering format. The instrument assesses characteristics of the school environment in an objective manner. When subjective characteristics such as ‘state of baseball field’, or ‘space in the bicycle parking’ were present, photographs were taken. The DOiT audit instrument was pretested for its reliability at two schools.

### Analyses

Our first aim is to evaluate the nationwide dissemination process of DOiT in the Netherlands All qualitative data systematically collected or observed during the study will be considered as data [29,30]. This means that not only information from in-depth interviews with teachers, but also all data reported during phone calls or observed during school visits will be included in the analysis. Regarding the interviews, a literal transcript of the audiotape of each interview will be written. All transcripts and other data will be marked with codes (open coding). The codes will be grouped into similar concepts in order to make them more workable, i.e. selective coding. Using tables and matrices, we aim to identify and compare facilitators and barriers around the key process indicators and implementation-related determinants. All quantitative data obtained from the logbooks and the teacher questionnaires collected during the study will be analysed in SPSS 20.0 (SPSS Inc. Chicago, Illinois, USA).

Our second study aim is to examine the relationship between quality of implementation and changes in students’ EBRBs and anthropometrics. The change in students’ EBRBs and anthropometrics will be analysed using multi-level linear regression analysis. We define three levels in our multi-level analyses: 1) student, 2) class, and 3) school. Analyses will be adjusted for baseline values, age, gender, ethnicity, and educational level. These variables will be checked as potential effect modifiers. Multilevel statistical analyses will be performed using MLwiN 2.22.

The process data, including information on level of dosage, level of fidelity and quality of delivery, will be combined into an ‘school implementation score’. Using linear regression analysis, we will examine the association between quality of implementation (implementation score) and program effect on EBRBs, as well as on anthropometrics. For all analyses a two-tailed significance level of <0.05 will be considered statistically significant.

In addition, we will explore the behavioural mediators of the intervention effect on BMI, waist circumference and sum of skinfolds using the product-of-coefficient method of MacKinnon [31]. We will specifically look at the mediating effects of consumption of sugar-containing beverages; consumption of high sugar/high fat snacks; sports participation; active transport; screen time and breakfast behaviour.

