*number of subjects required to conduct multi-level analyses with an estimated power of 90% and an alpha level of significance set at 0.05; sd = standard deviation based on the study of Singh et al. [12,13]; BMI = Body Mass Index.

In order to recruit control schools, we asked all intervention schools to provide the name of comparable schools in that area. As a result, we aimed to include control schools, matched on level of education, location (rural/urban area) and school size. Control schools did not implement DOiT during the study period. Regular contact with the management and teachers of control schools was ensured in order to promote their continued participation. Also the control schools received a short report of the research results upon completion.

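### The outcome model leaves out rural/urban location and school size, although control schools were matched on both

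*Protocol article*

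**What the plan says.** Under Study design and population, the effectiveness part is described as a cluster-controlled study whose control schools were "matched on level of education, location (rural/urban area) and school size". Recruitment of schools explains how they were found: "we asked all intervention schools to provide the name of comparable schools in that area". It adds: "As a result, we aimed to include control schools, matched on level of education, location (rural/urban area) and school size". The numbers of schools are given in the same section: "We aimed to include 20 DOiT implementation schools in the process evaluation", and for controls "Therefore, ten control schools were needed". The Discussion acknowledges that schools were not allocated at random.

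The Analyses section specifies the outcome model. Its structure is: "We define three levels in our multi-level analyses: 1) student, 2) class, and 3) school". Its covariates are: "Analyses will be adjusted for baseline values, age, gender, ethnicity, and educational level". The next sentence says that these same variables will be examined as possible effect modifiers. Location, school size and a matched-set term do not appear, and their absence is not explained.

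**The concern.** When a comparison is not randomised and the controls are chosen on named factors, those factors would normally be carried into the outcome model. This does two things. It corrects whatever imbalance the matching left behind, and it takes the variation between schools explained by those factors out of the error term. Here the design names three factors and the model keeps one.

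The second benefit matters because there are only 30 schools, so variation between schools weighs heavily on precision. The first matters because one control school out of ten moves the control arm's urban share by 10 percentage points, so a modest imbalance arises easily.

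The article itself treats these school features as relevant. School size is listed among the context factors (Table 3) and among the determinants of adoption. The school audit covers food outlets, sport facilities and bicycle parking, which could plausibly vary with location and size. What is at stake is the estimated effect of DOiT on BMI, the other anthropometric measures and the energy balance-related behaviours.

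**Working it through.** **Matching factors against model covariates**

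| Matching factor | In the adjustment list? |
|---|---|
| Level of education | Yes, as educational level |
| Location (rural/urban) | No |
| School size | No |

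**The plan's own figure.** Table 4 gives 510 students per group for BMI (SD 1.2, difference 0.25 kg/m², 90% power, two-sided 5%).

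- n = 2 × (1.960 + 1.282)² × 1.2² / 0.25² ≈ 485 per group.
- An SD of about 1.231, which prints as 1.2, gives 510, so rounding explains the gap.
- The other six rows come out at or within two of the stated number with the same formula: 80/80, 180/180, 238/238, 509/508, 115/115 and 42/40 (computed/stated).
- The formula contains no design effect, so Table 4 reveals no intraclass correlation (ICC) that could be used below. The present point does not depend on these sample sizes.

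**Precision (illustration).**

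- From the article: SD 1.2, difference 0.25, 20 and 10 schools.
- Assumed: 51 analysed students in every school (510/10), ICC of 0.01 to 0.05, and a share R² of the between-school variance explained by location and size. The class level is ignored.
- SE = √{ 1.2² × [ICC × (1 − R²) + (1 − ICC)/51] × (1/10 + 1/20) }
- Power = Φ(0.25/SE − 1.96). The SE without adjustment has R² = 0.

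| ICC | R² | SE without | SE with | Reduction | Power without → with |
|---|---|---|---|---|---|
| 0.01 | 0.1 | 0.0797 | 0.0783 | 2% | 0.88 → 0.89 |
| 0.01 | 0.3 | 0.0797 | 0.0755 | 5% | 0.88 → 0.91 |
| 0.01 | 0.5 | 0.0797 | 0.0726 | 9% | 0.88 → 0.93 |
| 0.02 | 0.1 | 0.0920 | 0.0897 | 3% | 0.78 → 0.80 |
| 0.02 | 0.3 | 0.0920 | 0.0847 | 8% | 0.78 → 0.84 |
| 0.02 | 0.5 | 0.0920 | 0.0794 | 14% | 0.78 → 0.88 |
| 0.05 | 0.1 | 0.1218 | 0.1172 | 4% | 0.54 → 0.57 |
| 0.05 | 0.3 | 0.1218 | 0.1076 | 12% | 0.54 → 0.64 |
| 0.05 | 0.5 | 0.1218 | 0.0971 | 20% | 0.54 → 0.73 |

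At R² = 0 nothing changes. If the 510 DOiT students are instead spread over 20 schools (25.5 each), the largest reduction falls slightly. At ICC 0.05 and R² 0.5, the variance factor without adjustment is (0.05 + 0.95/51)/10 + (0.05 + 0.95/25.5)/20 = 0.01123. With adjustment it is (0.025 + 0.95/51)/10 + (0.025 + 0.95/25.5)/20 = 0.00748. The ratio of standard errors is √(0.00748/0.01123) = 0.82, a reduction of 18%.

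**Bias (illustration).** Bias = (difference between arms in the share of urban schools) × (urban–rural difference in 20-month BMI change, given the covariates already in the model). Both inputs are assumed. Results are in kg/m², and the sign could go either way.

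| Imbalance | 0.05 | 0.10 | 0.20 | 0.30 |
|---|---|---|---|---|
| 0 points | 0 | 0 | 0 | 0 |
| 10 points | 0.005 | 0.01 | 0.02 | 0.03 |
| 20 points | 0.01 | 0.02 | 0.04 | 0.06 |
| 30 points | 0.015 | 0.03 | 0.06 | 0.09 |

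The last column assumes an urban–rural difference larger than the target effect itself, so 0.09 is a far corner of the table and not an expected value.

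**The case against.** Much of the case on the other side is right.

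- **The matching may have worked.** The study design section states the matching outright, and the word aimed appears only in the account of recruitment. Asking for comparable schools in the same area would tend to align location. Balance produced by matching still protects the estimate when the factors are left out of the model, and the usual consequence is a conservative standard error. This stands.
- **A 20:10 ratio is not a defect.** A reader might infer that matching must be imperfect because one-to-one pairs are impossible. The article never claims pairs, and 20:10 is compatible with two-to-one matching or balance by category.
- **Baseline values are in the model.** Differences in level linked to location or size are largely handled. Bias needs both residual imbalance and a link to change over 20 months, and the article gives no evidence of either.
- **Not all the precision is lost.** Educational level is retained, and the gain from the other two factors is nil if they are not prognostic.
- **The main limitation lies elsewhere.** The Discussion already discloses non-randomisation and adoption bias, which these two covariates would not remove.

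The omission itself remains. The article states an explicit adjustment list and gives no reason for dropping two of the three factors on which the controls were selected.

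**Conclusion.** The point holds as a mismatch between design and model. Residual imbalance in location or school size, if present and related to 20-month change, would not be corrected, and some precision may be forgone. It would be tempting to conclude that the effectiveness estimate is confounded or that the benefit of matching has been thrown away. The document does not support either, because no achieved balance is reported and both conditions for bias are unverified.

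The size cannot be derived from what is given and starts at zero. With an assumed ICC of 0.01 to 0.05 and up to half of the between-school variance explained, the standard error would fall by 0 to about 20%. With an assumed imbalance of up to 30 points and an urban–rural difference in change of up to 0.30 kg/m², the bias would be 0 to about 0.09 kg/m² against the 0.25 kg/m² target. The change is worth making because it is cheap and brings the model into line with the design.

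**What to change.** Add rural/urban location and school size as school-level fixed covariates in the three-level model for every effectiveness outcome, or state why they are left out. Say also whether they enter for adjustment only, since the plan checks its listed covariates as effect modifiers and ten control schools would support little in the way of interactions with school-level factors.

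Both variables were needed for the matching, so no new data should be required. Analyses were planned from September 2013, after data collection ended, so the list could be settled before they began.

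The cost is about two of the 28 school-level degrees of freedom (30 schools less two arms). If the factors are not prognostic, little is gained.

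A matched-area term should not be added unless it was recorded which intervention schools nominated which controls. The article describes no such sets, and up to ten of them entered as fixed effects could take up to nine of the 28 degrees of freedom.
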